### Blinding

Structural and functional MRI data will be qualitatively analysed by neurologists blinded to group allocation and order of assessments. Functional MRI training scan quality will be rated on region of activation, change over time and patterns of reorganisation. Data on the AHA and MUUL will be rated from video recordings masked and randomised.

### Adverse events

Any minor or major events associated with intervention or usual care groups will be screened at 20 weeks by open-ended questions. Any adverse events or unintended effects detected will be reviewed by the principal researchers RB, JZ and LM.

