### Study procedure

To account for children’s varying abilities to attend and concentrate and, to mitigate fatigue the following scheduling strategies will be used to maximise data integrity during baseline and follow up assessments. Families will be contacted prior to baseline assessments to ascertain whether they feel their child will need one or two days to complete assessments. All participants will attend The University of Queensland, St Lucia campus for all assessments, minimising travel. Neuropsychological testing will be scheduled first as this requires most attention and concentration by participants. Regular breaks will be scheduled for participants between assessments as necessary at baseline and follow-up appointments. All primary outcome clinical assessments will be performed prior to Magnetic Resonance Imaging (MRI). Extra time will be allocated at the start and end of each day to manage any unforeseen complications which may arise (e.g. travel/time delays and fatigue issues). Participants in the immediate intervention group will spend an additional day for Mitii™ training and return home with Mitii™ equipment to begin the 20 weeks intervention. After baseline assessments (T0), the waitlist group will continue care as usual for 20 weeks. All participants will then return to The University of Queensland after 20 weeks for a one to two day re-assessment (T1). The waitlist group will spend an additional day for Mitii™ training before returning home with equipment to commence the intervention. For each participant data will be collected at Baseline (T0). The immediate intervention group will have follow up assessments conducted immediately post-training at 20 weeks (T1) and retention at 40 weeks post-baseline assessments (T2). The waitlist group will have a second baseline assessment at 20 weeks (T1), post-intervention at 40 weeks (T2) and retention of effects at 60 weeks post-baseline assessments (T3).

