### Motivational strategies

Motivational strategies will be discussed during the initial Mitii™ training session with families and will include weekly performance feedback, positive re-enforcement by parents/guardians and incorporating Mitii™ into the regular family routine. Each participant will also have the option of using a rewards chart (child or adolescent version) broken up into four, five week blocks throughout the program as an additional motivational strategy (see Additional file 2 for child rewards chart). The rewards chart allows small rewards to be negotiated with the participants and their parents and/or guardians at the completion of each stage during the initial Mitii™ training. Program options such as physiotherapists demonstrating aerobic activities that are used during activity modules and including real-world images in figure ground, spatial relations, match two images and memory modules, are more likely to appeal to teenagers will be incorporated in their programs. One of the three virtual trainers will be assigned as the main contact for the participant and their family and remain in weekly contact. Families will be contacted weekly (or at the family’s request) to encourage ongoing engagement in the program. Once participants have completed the 20 weeks intervention they will receive a small reward provided by study personnel and parents will be asked to complete an exit questionnaire.

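### The one stated adverse event screen, at 20 weeks, falls before the waitlist group has used Mitii, so no systematic screen is stated for half of the planned exposure

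*Protocol article*

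**What the plan says.** The Adverse events section has two sentences. The first sets the time and method of collection: "Any minor or major events associated with intervention or usual care groups will be screened at 20 weeks by open-ended questions". The second sets the handling: "Any adverse events or unintended effects detected will be reviewed by the principal researchers". No other time for asking about harms is stated in the article.

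Study procedure gives the calendar for each group.

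- Immediate group: "The immediate intervention group will have follow up assessments conducted immediately post-training at 20 weeks (T1"), followed by a retention visit at week 40.
- Waitlist group, weeks 0 to 20: "After baseline assessments (T0), the waitlist group will continue care as usual for 20 weeks".
- Waitlist group, after the week 20 visit: "The waitlist group will spend an additional day for Mitii™ training before returning home with equipment to commence the intervention".
- Waitlist group, visits: "The waitlist group will have a second baseline assessment at 20 weeks (T1), post-intervention at 40 weeks (T2"), then a retention visit at week 60.

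There is other contact during training. Under Motivational strategies, "One of the three virtual trainers will be assigned as the main contact for the participant and their family and remain in weekly contact". The stated purpose of that contact is to keep the family engaged. The same section mentions an exit questionnaire for parents, without giving its content. The exit interview, in its own section, is about engagement with web-based therapy and runs only until the data are saturated.

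**The concern.** In a waitlist design every child eventually receives the intervention, so safety information on exposed children can in principle come from the whole sample. A screen fixed at 20 weeks after baseline collects it from the immediate group only. For the waitlist group the screen describes 20 weeks of usual care and ends before its exposure begins.

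This matters because the training is done at home under parental supervision, by children whose injury often affects balance, strength and coordination (Background). Difficulty is adjusted upward over time (Mitii intervention), and weights, wobble discs and stepping blocks are supplied to add challenge (Equipment). Minor events such as a stumble or muscle soreness are the kind that families may not volunteer unless asked. The Discussion describes the trial as the largest of its type in this population, so its count of screened exposed children is worth having in full.

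**Working it through.** **Inputs.** Sixty children, 30 per group (Abstract); 20 weeks of training per child, 30 minutes a day, six days a week (Abstract); the screen at week 20 (Adverse events); training in weeks 0 to 20 for the immediate group and weeks 20 to 40 for the waitlist group (Study procedure).

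**The plan's own figure.** Dose per child: 0.5 h × 6 days × 20 weeks = 60 h, as the article states. The article gives no safety figure to reproduce.

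**Screen against exposure.**

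| Group | Mitii weeks | Exposure weeks completed at the week 20 screen | Stated screen at end of training |
|---|---|---|---|
| Immediate | 0–20 | 20 of 20 | Yes (T1) |
| Waitlist | 20–40 | 0 of 20 | None stated (T2) |

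**Exposure covered.** Child-weeks screened: 30 × 20 = 600. Child-weeks planned: 60 × 20 = 1,200. Coverage: 600 / 1,200 = 50%. In potential training hours: 30 × 60 = 1,800 of 60 × 60 = 3,600.

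**Zero-event bound.** If no event is seen in n exposed children, the exact one-sided 95% upper bound on risk is 1 − 0.05^(1/n).

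| Exposed children screened | Basis | Upper bound |
|---|---|---|
| 30 | one group, no dropout | 9.5% |
| 60 | both groups, no dropout | 4.9% |
| 29 | one group, at the completers required for AMPS | 9.8% |
| 58 | both groups, same basis | 5.0% |
| 26 | one group, at the completers required for sit-to-stand | 10.9% |
| 52 | both groups, same basis | 5.6% |

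**Chance of seeing at least one event**, 1 − (1 − p)^n. The article gives no event risk, so p is an assumption shown over a range.

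| Assumed risk p | n = 30 | n = 60 |
|---|---|---|
| 2% | 45.5% | 70.2% |
| 5% | 78.5% | 95.4% |
| 10% | 95.8% | 99.8% |

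**Could week 20 be counted from each group's own start of training?** That reading would close the gap, but the text does not support it. The Adverse events sentence places the usual care group at the same screen, and usual care is what the waitlist group receives in weeks 0 to 20. Study procedure counts from baseline and puts the end of the waitlist group's training at week 40.

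**The case against.** The strongest defence is that 20 weeks is the right time for the trial's main question. It is the primary endpoint and the only point at which Mitii can be compared with concurrent usual care. That stands: the randomised harms comparison loses nothing. The hypotheses also set no safety objective or precision target, so no stated aim fails, and the bounds above illustrate the loss rather than test it against a requirement.

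It can also be said that a condensed article leaves event reporting to the full protocol. That holds for ongoing reporting and escalation, but not for the screening time, which the article fixes.

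Three stronger readings are tempting and go beyond the text.

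- **That waitlist children are never asked about harms, or that half the exposure yields no safety data.** The article does not say the week 20 screen is the only enquiry. A named trainer is in weekly contact during training, parents supervise, and an exit questionnaire follows the 20 weeks. None of these is described as a harms screen, but spontaneous reports are possible. The text supports only that no systematic screen is stated for that exposure.
- **That events would reach the reviewers months late.** The article says detected events are reviewed. It does not tie review to week 20, and its silence on reporting flow is not evidence of delay.
- **That the weekly calls should carry a harms question.** In weeks 0 to 20 only the immediate group would be prompted. That could sharpen its recall at T1 relative to the waitlist group, even with an identical T1 form, and so bias the one randomised comparison of harms.

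**Conclusion.** The point holds in limited form. The article fixes a screening time that, followed as written, systematically covers 30 of 60 planned exposed children and 600 of 1,200 child-weeks. This is a stated rule that misses the waitlist group's training period, not a detail left to a fuller document. The cost in precision is an upper bound of 9.5% in place of 4.9% when no events are seen.

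These figures assume that all 60 children train as planned, that no spontaneous reports are counted, and, for the pooled bound, that risk is the same in both groups. Dropout to the completer numbers in the sample size section changes the bounds little. The efficacy analysis and the T1 harms comparison are not touched. The loss is confined to systematic, uncontrolled safety information on exposed children, so this is worth amending but does not threaten the trial's main conclusions.

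**What to change.** Amend the Adverse events section so that the open-ended questions asked at T1 are also asked of the waitlist group at its existing T2 visit (week 40, end of training).

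State how the data will be used:

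1. The T1 screen, asked identically in both groups, remains the only between-group comparison of harms.
2. The immediate group's T1 answers and the waitlist group's T2 answers are reported together as a pooled, uncontrolled summary of Mitii exposure.

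Do not add weekly harms prompting in one group during weeks 0 to 20.

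The cost is one short form for up to 30 families at a visit already planned. It needs no new visit or staff. Screened exposure rises from 600 to 1,200 child-weeks.

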### Study procedure

To account for children’s varying abilities to attend and concentrate and, to mitigate fatigue the following scheduling strategies will be used to maximise data integrity during baseline and follow up assessments. Families will be contacted prior to baseline assessments to ascertain whether they feel their child will need one or two days to complete assessments. All participants will attend The University of Queensland, St Lucia campus for all assessments, minimising travel. Neuropsychological testing will be scheduled first as this requires most attention and concentration by participants. Regular breaks will be scheduled for participants between assessments as necessary at baseline and follow-up appointments. All primary outcome clinical assessments will be performed prior to Magnetic Resonance Imaging (MRI). Extra time will be allocated at the start and end of each day to manage any unforeseen complications which may arise (e.g. travel/time delays and fatigue issues). Participants in the immediate intervention group will spend an additional day for Mitii™ training and return home with Mitii™ equipment to begin the 20 weeks intervention. After baseline assessments (T0), the waitlist group will continue care as usual for 20 weeks. All participants will then return to The University of Queensland after 20 weeks for a one to two day re-assessment (T1). The waitlist group will spend an additional day for Mitii™ training before returning home with equipment to commence the intervention. For each participant data will be collected at Baseline (T0). The immediate intervention group will have follow up assessments conducted immediately post-training at 20 weeks (T1) and retention at 40 weeks post-baseline assessments (T2). The waitlist group will have a second baseline assessment at 20 weeks (T1), post-intervention at 40 weeks (T2) and retention of effects at 60 weeks post-baseline assessments (T3).

### Equipment

The Mitii™ intervention requires no specialist resources. All participants will receive a Microsoft Kinect®, laptops and pre-paid internet dongles for families who are unable to access a computer and/or internet at home for the 20 weeks intervention period. If families experience any technical issues, a study telemedicine engineer will be available to troubleshoot any technical difficulties. Step blocks, wobble discs and weights are also provided to families as an additional challenge for tasks as they progress through the program.

### Mitii™ intervention

Following occupational therapy, physiotherapy, neuropsychology and neurovascular assessments the participants and their parents will complete the Mitii™ training in preparation to start 20 weeks of intervention. Firstly, a therapist will deliver a lecture to explain the background and purpose of Mitii™, how the program works (see Additional file 1 for the participant manual) and motivational strategies to encourage engagement in the program (see Additional file 2 for child rewards chart). Children will then receive individualised training in how to use the Mitii™ program based on their capacity in baseline assessments. Therapists will select between an easy, moderate or difficult version addressing unilateral (right or left) or bimanual UL and LL deficits. A de-identified Mitii™ account will be created using an alias profile for each participant which will allow the program to be downloaded from the internet (https://mitiistorage.blob.core.windows.net/vsdeploy/clickonce/publish.htm) for each participant. Once the program has downloaded, the child will then able to log onto the program to complete their training at home or local environment at their convenience. The program will be requested to be completed six days a week for 20 weeks. This will provide a minimum potential treatment dose of 60 h. The participant should be appropriately supervised by a parent/guardian (according to their age) to ensure activities are being completed safely and correctly.

Once the participants and their parents have returned home, the three virtual trainers (one occupational therapist, one physiotherapist and one neuropsychologist) will develop an individually tailored program from the 12 available modules including; (1) gross motor or physical activity (e.g. repetitive sit-to-stand exercises); (2) combined cognitive and visual perception and; (3) UL (e.g. moving the UL to solve a mathematic equation) (See Additional file 3). Modules will be combined in sequence to make a daily program of approximately 30 min duration. To ensure each participant receives a similar training program, all daily programs will comprise of approximately 40 % gross-motor and 60 % cognitive-UL training modules.

The three virtual trainers will together evaluate each participant’s performance on a weekly basis and adjust module content variables to maintain the program at an appropriate level of difficulty or intensity to promote a training effect. Therapists access each participant’s program remotely via the Mitii™ user interface “Cockpit” and can monitor how frequently the participant has logged into Mitii™, how long they have spent engaged in the program, games that have been skipped and progress in each module. The complexity of the modules can be adjusted by increasing or decreasing the level of difficulty of visual perceptual (images graded on a colour code system of blue-green-red-black), cognitive (e.g. increasing the length of a memory sequence) and motor activities (e.g. reducing the base of support for balance).

### Motivational strategies

Motivational strategies will be discussed during the initial Mitii™ training session with families and will include weekly performance feedback, positive re-enforcement by parents/guardians and incorporating Mitii™ into the regular family routine. Each participant will also have the option of using a rewards chart (child or adolescent version) broken up into four, five week blocks throughout the program as an additional motivational strategy (see Additional file 2 for child rewards chart). The rewards chart allows small rewards to be negotiated with the participants and their parents and/or guardians at the completion of each stage during the initial Mitii™ training. Program options such as physiotherapists demonstrating aerobic activities that are used during activity modules and including real-world images in figure ground, spatial relations, match two images and memory modules, are more likely to appeal to teenagers will be incorporated in their programs. One of the three virtual trainers will be assigned as the main contact for the participant and their family and remain in weekly contact. Families will be contacted weekly (or at the family’s request) to encourage ongoing engagement in the program. Once participants have completed the 20 weeks intervention they will receive a small reward provided by study personnel and parents will be asked to complete an exit questionnaire.

### Data management

Data will be recorded and managed through a confidential online database run through the Queensland Cerebral Palsy and Rehabilitation Research Centre (QCPRRC). Participants will also have paper files which will be de-identified and only contain the participant’s unique identification code. These files will be stored in a locked filing cabinet at the QCPRRC separate from files containing participant demographic and consent information. The Mitii™ program, participants’ Mitii™ scores and training history will be stored on a secure server at the Microsoft Azure Data Centre in Ireland. In addition to Microsoft’s standard data procedures, the Mitii™ program and associated data will be backed up every two weeks. To ensure participants’ confidentiality, participants will not have personal information or details recorded on the program. Participants will use a non-identifying “alias” name to log into Mitii™ and study personnel will use their personal email (not linked to the Mitii™ program) for correspondence.

## Classification measures

### Australasian Rehabilitation Outcome Centre (AROC) impairment codes

Classification of the ABI will be made according to the AROC impairment codes [64]. The AROC impairment codes describe the reason for rehabilitation according to impairment groups. Episodes are classified according to the primary reason for the current episode of rehabilitation care. In total, there are sixteen impairment groups. Two groups relate to rehabilitation episodes for children with ABI – Stroke and Brain Dysfunction. Firstly, the Stroke impairment group can be subdivided into two sub-groups, “Haemorrhagic” and “Ischaemic”. These sub-groups are then further subdivided into individual group codes. Secondly, Brain Dysfunction can be divided into two sub-groups including, “Non-traumatic” and “Traumatic”. Non-traumatic brain dysfunction codes include subarachnoid haemorrhage (2.11), anoxic brain damage (2.12) and other non-traumatic brain dysfunction (2.13). Examples of other non-traumatic brain dysfunction include brain injury as a result of tumour, encephalitis or complications of ventriculoperitoneal shunt revisions. Traumatic brain dysfunction codes can be open (2.21) or closed injury (2.22). A rehabilitation consultant from QPRS will classify all participants according to these impairment codes.

### Classification of the brain lesion

The nature of the brain lesion will be classified on sMRI using both a qualitative description [66] and semi-quantitative scale for classification of brain lesion severity for children with ABI [67, 68].

Structural MRI will be obtained for each child using a 3 Tesla (3T) Magnetom (Siemens) scanner using T1-weighted high resolution 3D MPRAGE, T2-weighted FSE and 3D FLAIR sequences. Structural MRI will be evaluated by a paediatric neurologist (SF who will be blinded to clinical and medical history) to describe the type of lesion and presumed pathogenic pattern (e.g. stroke, hypoxia/anoxia, toxic, metabolic or infective injuries and head trauma).

The brain lesion severity will be determined by using a semi-quantitative scale designed for classification of brain lesion severity in children with CP [67]. The semi-quantitative scale has demonstrated high inter-rater and intra-rater reliability [67]. According to the scoring system, the brain lesion is represented on a graphical template and raw scores for lobes, subcortical structures (basal ganglia, thalami and brainstem), corpus callosum and cerebellum are systematically calculated, where higher scores represent more severe pathology. Each hemispheric score (HS) is the sum of the lobar scores (maximum score of 12). The basal ganglia and brainstem score (BGBS) is the sum of left and right subcortical structures (basal ganglia, thalamus, brainstem and posterior limb of the internal capsule) (maximum score of 10). The global score (GS) is the sum of the right and left HS, BGBS, corpus callosum and cerebellum scores (maximum of 40). A laterality index (LI) will be calculated for each scan (range 0–1) to determine the lateralisation of the lesion, assuming the HS as the lateralised measure. A score approximating 0 indicates a more bilateral lesion; a score approaching 1 more unilateral involvement. Preliminary to further analysis, reliability will be tested in children with an ABI.

### Classification of brain injury severity

Where possible, available information will be collected from the participant’s medical records regarding their initial brain injury as these may have a prognostic effect. Information will include Glasgow Coma Scale (GCS) at the time of injury or admission; in the instance of a TBI length of Post Traumatic Amnesia (PTA), loss of consciousness (LOC) and duration of coma; treating hospital and length of hospitalisation; additional injuries or complications at time of injury and the Functional Independence Measure for Children (WeeFIM) at the time of discharge [69–71].

A description of comorbidities (e.g. orthopaedic injury, epilepsy, psychological and pre injury status) and any other treatments and interventions (e.g. surgical, medical or radiation) will be collected on an entry questionnaire completed by the parent. Information regarding the participant’s school grade and involvement in a special education program will also be collected in the same baseline questionnaire.

